### Study Setting

A diverse population resides in Rawalpindi, with varying socioeconomic backgrounds and cultural identities, making it a suitable place to assess the effect of a client-centered counseling approach on FP uptake. The study trial is conducted at tertiary care hospitals and their affiliated FHCs. Rawalpindi has an extensive network of nearly 60 FHCs that are administratively affiliated with tertiary hospitals.

### Study Timeline

The study trial will be conducted over a time frame of 8 to 9 months. Figure 2 provides a detailed timeline of all the trial activities, including a standardized schedule for participant enrollment, the interventional phase, and the postinterventional assessment.

**Figure 2. F2:**
[figure not shown]
SPIRIT (Standard Protocol Items: Recommendations for Interventional Trials) timeline of the study. GATHER: greet, ask, tell, help, explain, return.

### Sampling Methods and Sample Size Calculation

#### Consecutive Sampling of Clients

In this initial phase, all eligible clients visiting selected tertiary care hospital–affiliated FHCs will be enrolled through nonprobability consecutive sampling. The sample size for this phase was calculated using the WHO sample size calculator [24], with a margin of error of 0.05, 95% CIs, and assumed prevalence of modern contraceptive uptake of 27%, as reported for Punjab in the Pakistan Demographic and Health Survey 2017‐18. A sample size of 333 participants was calculated using these parameters.

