#### Study Participants: Purposive Sampling and Sample Size Calculation

For the final phase of the trial, women of reproductive age visiting FHCs for FP services will be recruited through purposive sampling to compare client satisfaction and uptake of modern contraceptive methods before and after the intervention. The sample size estimate considered feasibility and the ability to inform future scale-up studies covering larger populations.

Baseline modern contraceptive uptake in all arms was assumed to be approximately 25% based on estimates from the Pakistan Demographic and Health Survey 2017‐18. A collective review of systematic reviews and meta-analyses revealed that improved counseling strategies can increase contraceptive uptake up to 30% to 40%, corresponding to an absolute increase of nearly 8% to 18% in comparison to routine care [23]. Based on the above evidence, we assumed values of 25% and 40% for contraceptive uptake in the control and interventional arms, respectively. An absolute effect size of 15% or 0.15 points was assumed for this study.

The sample size was calculated using a standard formula for comparing 2 populations through testing the 1-sided hypothesis. The significance level was set at 5% (α=.05) for a power of 80% (1−β=0.80). Given the design of the study, a pragmatic approach was used. Consistent with values reported in health services literature, an intracluster correlation coefficient (ICC) of 0.02 [25] and design effect of 1.38 (DE=1+(m-1) x ICC) was applied. Following methodological guidance for pilot trials, the sample size was not inflated to meet confirmatory power requirements, and a sample size of 60 per arm and 180 across all 3 arms was chosen.

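### The stated inputs for the baseline sample give 303, not 333, and separately the ±5-point margin makes no allowance for clustering by hospital catchment

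*Protocol article*

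**What the plan says.** The section Consecutive Sampling of Clients sizes the baseline phase as a single-prevalence survey. It says "The sample size for this phase was calculated using the WHO sample size calculator", "with a margin of error of 0.05, 95% CIs" and an "assumed prevalence of modern contraceptive uptake of 27%, as reported for Punjab", and concludes: "A sample size of 333 participants was calculated using these parameters". It names no nonresponse allowance, finite population correction or design effect.

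On recruitment, the same section says that "all eligible clients visiting selected tertiary care hospital–affiliated FHCs will be enrolled through nonprobability consecutive sampling". Study Design makes the hospital catchment the unit of clustering, with the family health centers of one hospital counted as a single cluster.

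The later section on sampling of study participants, which covers the 180-client comparison, takes an ICC of 0.02 and a "design effect of 1.38". Nothing comparable is applied to the 333.

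Data Collection and Analysis lists t tests, ANOVA and χ² tests for exploratory comparisons. It then sets out mixed models with a catchment random intercept, and GEE as a sensitivity analysis, for the outcomes of the interventions.

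**The concern.** There are two separate problems. First, the article states a calculation and its result, and the two disagree. A reader who repeats the calculation cannot tell whether an input was misreported or an allowance left out.

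Second, the formula treats the clients as a simple random sample from one population, whereas they come in groups from hospital catchments. The article itself expects women in the same catchment to resemble one another, because it adjusts the other sample for this. On the same assumption, 333 clustered clients carry less information than 333 independent ones, and the planned ±5 points is optimistic.

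The baseline sample serves two purposes: it is the reference against which later change is judged (Phase 1), and it supports a cross-sectional analysis of factors associated with contraceptive use and discontinuation (Study Aim). Intervals and tests that ignore catchments would make both look more certain than they are.

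**Working it through.** **Inputs.** From Consecutive Sampling of Clients: p = 0.27, d = 0.05, 95% confidence (z = 1.96), stated n = 333. From the sample size section for the 180 clients: ICC = 0.02, design effect (DE) = 1.38, with DE = 1 + (m − 1) × ICC. The number of hospital catchments, k, is not given, so it is varied below.

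**Step 1: reproduce the stated figure.**

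n = z² p(1 − p) / d² = 1.96² × 0.27 × 0.73 / 0.05² = 302.9, so 303.

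The stated 333 is 30 higher (30/303 = 10%).

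**Step 2: look for a route to 333.**
- Same inputs, other methods: continuity correction 323, Wilson 301, arcsine about 319, Clopper-Pearson about 320, one-sided 214, 99% confidence 524. A finite population correction only lowers n.
- Other prevalences in the article: 25% gives 289, 34.3% gives 347, 35.5% gives 352.
- Back-solving: 333 needs a prevalence of about 31.6–31.7%, or a margin of 0.0477.
- A 10% addition: 303 × 1.10 = 333.3, which fits. Dividing by 0.90 gives 337, which does not.

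So no standard method reproduces 333 from the stated inputs alone. An unstated 10% addition is the simplest match.

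**Step 3: precision of 333 without clustering.**

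1.96 × √(0.27 × 0.73 / 333) = 0.0477, or ±4.8 points. This is slightly better than the target.

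**Step 4: precision with clustering.**

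Margin = 1.96 × √(0.27 × 0.73 × DE / 333).

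At the article's DE of 1.38, the effective sample size is 333 / 1.38 = 241 and the margin is 0.0560, or ±5.6 points. Reaching ±5 points at that DE would take 302.9 × 1.38 = 418 clients. A DE of 1.38 at ICC 0.02 corresponds to m = 1 + 0.38/0.02 = 20 clients per catchment.

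With ICC 0.02 and k equal catchments, m = 333/k:

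| k (assumed) | m | DE | Effective n | Margin (points) |
|---|---|---|---|---|
| 3 | 111 | 3.20 | 104 | ±8.5 |
| 6 | 55.5 | 2.09 | 159 | ±6.9 |
| 9 | 37 | 1.72 | 194 | ±6.3 |
| 12 | 27.75 | 1.54 | 217 | ±5.9 |
| 20 | 16.65 | 1.31 | 254 | ±5.5 |

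**Step 5: when would ±5 points hold?**

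Break-even DE = 333 / 302.9 = 1.10, so m = 1 + 0.0995/0.02 = 6.0 and k = 333 / 5.98, about 56 catchments. Study Setting counts close to 60 family health centers in total, and these are grouped under hospitals, so 56 or more hospital catchments is not plausible.

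**The case against.** The strongest reply is that little depends on this. The 0.05 margin is a planning input, not a claim about achieved precision. It enters no test of effect, and recruitment of the 333 is complete, so the final interval will come from the data. The number of catchments is unknown and the ICC is borrowed from another calculation, so the size of the shortfall is conditional. The plain tests are labeled exploratory. The section on quantitative and qualitative analysis repeats the commitment to allow for the clustered design when intervention effects are assessed, and an article may leave baseline detail to the full plan.

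Most of this stands, and it limits the point to reporting and precision. It does not rescue the sentence that derives 333 from three inputs that give 303. Nor does it change the direction of the clustering effect, which is the same for any plausible number of hospitals. The commitment to clustered analysis is written for intervention outcomes, and the article does not carry it over to the baseline determinants.

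A reader might infer more than the documents support:
- **That the wrong figure causes the loss of precision.** It does not. The mismatch is in the safe direction (±4.8 points), and the loss comes only from clustering.
- **That 333 is known to be 303 plus 10%.** The multiplication fits, but no allowance is documented.
- **That there are nine catchments.** This can be back-solved (m = 20 and 180/20 = 9), but the article states neither figure.
- **That plain χ² tests at a nominal 5% have a true error near 13.5%.** The calculation, 2 × (1 − Φ(1.96/√1.72)) = 0.135, needs nine catchments and a factor constant within each catchment. It does not carry over to individual-level factors such as age, parity or education.

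**Conclusion.** The point holds in two separate parts.

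1. **Certain:** the stated inputs give 303, so the article's derivation of 333 is wrong as written. This is a reporting error with no cost in precision.
2. **Firm in direction, conditional in size:** the planned ±5 points ignores clustering. The margin is about ±5.6 points at the article's own DE of 1.38, and about ±5.5 (20 catchments) to ±8.5 (3 catchments) at ICC 0.02. This assumes that the ICC chosen for the 180-client comparison also applies at baseline and that catchments contribute equal numbers.

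Neither part touches the power of the primary comparison, which rests on the separate 180-client calculation.

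**What to change.** - State 303 as the result of the three inputs. If an allowance was added to reach 333, declare it and its size; if not, correct the figure or the inputs.
- Replace the ±5-point precision with the cluster-adjusted margin for the actual number of catchments, naming that number and the ICC used.
- Report the baseline prevalence with a cluster-adjusted confidence interval. For the cross-sectional analysis of determinants, use the catchment random-intercept or GEE models already planned for the intervention outcomes, in place of plain χ² and ANOVA tests.

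The cost is a few sentences and a modest change to the baseline analysis. No further clients are needed. The one drawback is a less favorable stated precision.

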#### Stratified Random Sampling of Centers

Stratified random sampling of urban and rural locations was used in the second phase of the trial. FHCs affiliated with tertiary care hospitals were stratified by geographical location, followed by randomization through the lottery method into 3 study arms (one control arm and two interventional arms) to maintain objectivity and reduce selection bias.

#### Service Providers: Universal Sampling

All service providers were enrolled in the trial through universal sampling. Eligible service providers had at least 6 months of experience in contraceptive counseling, were directly involved in FP service delivery, and were willing to participate through to completion of the study. For uniformity across the study arms, each arm enrolled 18 to 24 service providers for later training specific to their allotted arm. The total sample will thus be 36 to 48 service providers across both interventional arms, allowing adequate representation of service providers and assessment of the effect of training on the service providers’ competency and ability to promote contraceptive uptake.

#### Study Participants: Purposive Sampling and Sample Size Calculation

For the final phase of the trial, women of reproductive age visiting FHCs for FP services will be recruited through purposive sampling to compare client satisfaction and uptake of modern contraceptive methods before and after the intervention. The sample size estimate considered feasibility and the ability to inform future scale-up studies covering larger populations.

Baseline modern contraceptive uptake in all arms was assumed to be approximately 25% based on estimates from the Pakistan Demographic and Health Survey 2017‐18. A collective review of systematic reviews and meta-analyses revealed that improved counseling strategies can increase contraceptive uptake up to 30% to 40%, corresponding to an absolute increase of nearly 8% to 18% in comparison to routine care [23]. Based on the above evidence, we assumed values of 25% and 40% for contraceptive uptake in the control and interventional arms, respectively. An absolute effect size of 15% or 0.15 points was assumed for this study.

The sample size was calculated using a standard formula for comparing 2 populations through testing the 1-sided hypothesis. The significance level was set at 5% (α=.05) for a power of 80% (1−β=0.80). Given the design of the study, a pragmatic approach was used. Consistent with values reported in health services literature, an intracluster correlation coefficient (ICC) of 0.02 [25] and design effect of 1.38 (DE=1+(m-1) x ICC) was applied. Following methodological guidance for pilot trials, the sample size was not inflated to meet confirmatory power requirements, and a sample size of 60 per arm and 180 across all 3 arms was chosen.

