### Study Phases

#### Phase 1: Formative and Baseline Assessment

Phase 1 is primarily meant for desk review and baseline assessment of uptake patterns of modern contraception, along with the determinants of discontinuation within 6 months at the FP service delivery points across the district. Mapping of existing counseling strategies used by the service providers to support contraceptive uptake was done through an extensive literature review in the initial phase [26]. The data collected in this phase will be considered as a point of reference for evaluating the effectiveness of the interventions.

Women of reproductive age seeking FP services or who have recently started using contraception were enrolled. Women visiting centers for emergency contraception or who discontinued use due to systemic illness were excluded from the study.

A pretested, structured questionnaire comprising demographics, reproductive history, contraceptive use, and service use was used for collecting data. Key variables included currently used contraceptive methods, duration of use, reasons for selection, and factors contributing to discontinuation (if applicable). Additionally, facility records from selected centers were reviewed to validate the client-reported data and assess aggregate service use metrics.

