##### Randomization and Blinding

Cluster randomization was conducted at the hospital level, with each hospital constituting a cluster. Hospitals with similar characteristics were grouped to maintain comparability, and randomization was performed using computer-generated methods, with stratification to balance key variables such as hospital size and patient demographics. This strategy helps in minimizing contamination and bias in allocation.

For the interventional phase, the interventional arms are implementing the standardized counseling approach for which they were trained, whereas the control arm continues routine practices. Clients will remain blinded to the counseling approach they are provided, but owing to the nature of the interventions, the service providers know which arm they are assigned to. Although this is a study design limitation, it is standard practice in behavioral interventional trials.

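### Women supplying the primary outcome are to be recruited purposively after allocation, while the baseline reference sample was consecutive, so selection can differ by arm

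*Protocol article*

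**What the plan says.** The protocol article gives two sampling rules for clients.

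- **Baseline** (Consecutive Sampling of Clients): "all eligible clients visiting selected tertiary care hospital–affiliated FHCs will be enrolled through nonprobability consecutive sampling". The target was 333. The Phase 1 section gives these data a role in the effect estimate: "The data collected in this phase will be considered as a point of reference for evaluating the effectiveness of the interventions".
- **Outcome sample** (Study Participants: Purposive Sampling and Sample Size Calculation): "women of reproductive age visiting FHCs for FP services will be recruited through purposive sampling to compare client satisfaction and uptake" of modern methods before and after the intervention. The size is 60 per arm, 180 in all. Uptake is the primary outcome and client satisfaction a secondary one (Study Outcomes).

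On allocation and masking, Randomization and Blinding says "Cluster randomization was conducted at the hospital level, with each hospital constituting a cluster" and "owing to the nature of the interventions, the service providers know which arm they are assigned to". Clients are blinded.

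The Results section dates recruitment of the 333 clients to July 20–31, 2025, and face-to-face training to July 31–August 3. It schedules the post-intervention waves for October 2025 and for December 2025 to January 2026.

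Data Collection and Analysis takes outcomes from facility records and client exit interviews. It plans mixed models, difference-in-differences, and adjustment for age, parity, education, baseline contraceptive use and facility characteristics.

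**The concern.** Randomising hospitals balances hospitals. It does not govern which women within a hospital are later chosen to supply the outcome. Purposive sampling leaves that choice to someone's judgement, and here it is made once the arms are known at the sites. If receptive or satisfied clients are chosen more readily in a trained arm than in the control arm, the arm contrast in uptake and satisfaction mixes selection with the effect of GATHER or the BCS.

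The sampling rule also changes between the reference wave and the outcome waves. A simple before-after comparison would then reflect the change of rule as well as any change in practice.

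The stakes are the primary outcome and one secondary outcome. Selection of this kind cannot be reliably undone in the analysis once the data are in.

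**Working it through.** **1. Order of events.** The article gives no randomisation date, but training was specific to each arm, so allocation was settled by the start of training on July 31, 2025. Outcome collection starts in October 2025. Women recruited for those waves are therefore chosen after allocation. The same holds if the 180 are drawn from the 333 baseline women once training has begun: 180/333 = 54% would be kept and 153 left out by judgement.

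**2. What each safeguard covers.**

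| Safeguard in the article | What it handles | What it leaves open |
|---|---|---|
| Cluster randomisation | Which hospital is in which arm | Which women within a hospital are chosen afterwards |
| Client blinding | Clients' reporting of satisfaction | Conduct of whoever selects |
| Covariate adjustment | Measured differences; baseline use helps in part if recorded on arrival | Receptiveness, satisfaction and other unmeasured traits |
| Difference-in-differences | Differences stable over time, or shifts common to all arms | A sampling change that acts differently by arm |

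The article mentions reducing selection bias only for the allocation of centres (Stratified Random Sampling of Centers).

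**3. Planned effect.** From the sample-size section: control 25%, intervention 40%, so 40 − 25 = 15 points. The odds ratio is (0.40/0.60)/(0.25/0.75) = 2.0.

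**4. Illustration A: selection in one arm only, no true effect.** Let f be the excess share of women selected in an active arm who would take up a method anyway. The document gives no value for f.

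Apparent uptake = (1 − f) × 0.25 + f × 1.0, so shift = 0.75 × f.

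- f = 10% (6 of 60 women): 0.75 × 0.10 = 7.5 points, half the planned effect.
- f = 20% (12 of 60 women): 0.75 × 0.20 = 15 points, the whole planned effect.

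**5. Illustration B: the same question, modelled differently.** Let r be the relative chance that a user rather than a non-user is picked, in one arm only. This is also assumed.

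Apparent uptake = 0.25r/(0.25r + 0.75).

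| r | Apparent uptake | Spurious difference |
|---|---|---|
| 1.0 | 25.0% | 0 |
| 1.25 | 29.4% | 4.4 points |
| 1.5 | 33.3% | 8.3 points |
| 2.0 | 40.0% | 15 points |

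**6. Selection that is equal in all arms.** With the same f everywhere, each arm's uptake p becomes p + f(1 − p), and the arm difference becomes (1 − f) times the true one. At f = 10%, a true 15 points reads as 0.9 × 15 = 13.5. With no true effect the arm difference stays at zero. The control arm would nevertheless show a before-after rise of 7.5 points with no real change. Equal selection therefore largely cancels between arms but distorts before-after comparisons.

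**The case against.** **Who selects.** A reader might infer that arm-aware providers hand-pick the women. The article does not say so: it documents that providers know their arm, and is silent on who approaches clients and whether that person is masked. The purpose behind the sampling may be no more than reaching women of reproductive age who attend for family planning. This stands as a limit. The risk comes from the stated sampling rule, not from evidence of misuse.

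**Different eligibility.** One might also read the baseline as a different population, because the Phase 1 section reports: "Women of reproductive age seeking FP services or who have recently started using contraception were enrolled". The documents do not support that. The Phase 1 exclusions are worded as exclusions from the study, the sample-size section states no competing criteria, and a recent starter can also be a woman attending for family planning. Only the sampling methods demonstrably differ.

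**Cohort or new attendees.** Adjustment for baseline contraceptive use, the follow-up assessments, and loss to follow-up given as a reason for missing data all suggest that women are followed. Recruitment in the future tense, exit interviews at every time point, and 333 versus 180 women suggest separate samples. The before-and-after wording could even mean that some baseline women are purposive. If all consecutively enrolled women were followed, the mismatch would disappear. A purposive subset chosen after allocation would not remove the risk.

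**Covariates and records.** It would be too strong to say that no covariate helps: baseline use can help in part. Facility records are a second data source, but the article does not say that they replace the recruited women for the primary outcome.

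**Pilot status.** The trial is labelled a pilot and the 60 per arm is openly not sized for confirmatory power. That softens the consequence. The article still aims to evaluate effectiveness, plans significance tests, and claims strong internal validity under Strengths. A small sample does not excuse an avoidable bias.

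**Conclusion.** The point holds as a risk created by a stated rule. The outcome women are to be chosen purposively, after allocation, at sites where providers know their arm, while the reference sample was consecutive. Selection that differs by arm would bias the uptake and satisfaction contrasts, and the planned analysis would not reliably remove it. A change in sampling that is equal across arms would largely cancel between arms but would distort simple before-after comparisons.

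Neither size nor direction can be derived from the document. The 7.5 and 15 points rest on assumed values of f, on selection confined to one active arm, and on certain uptake among the excess women. They show that modest selection could match the planned effect, not that it will. The conclusion does not depend on who recruits, or on whether the women are new or drawn from baseline, provided that the draw is purposive and follows allocation.

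**What to change.** - In Study Participants: Purposive Sampling and Sample Size Calculation, replace purposive with consecutive sampling for the client outcome samples at 3 and 6 months. If a cohort is intended, say so and follow all consecutively enrolled baseline women.
- Apply the Phase 1 inclusion and exclusion criteria identically at every wave and in every arm.
- Have the existing exit-interview data collectors approach eligible clients in order, and keep a count of those approached and those refusing.
- Keep purposive sampling for the qualitative interviews and focus groups in Phase 3 only.

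The cost is a change of protocol wording and a simple log, and the target numbers may take slightly longer to reach. An analysis among women not using a modern method on arrival may be added as supporting, since current method is already on the questionnaire. It should not replace the primary outcome, because it would change the question asked and shrink a sample of 60 per arm.

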## Methods

### Study Framework

The theory of change construct will be used in this study. Using this theory enables interventions to improve client satisfaction and service provider competency through training and measure these improvements in terms of behavioral change, thereby making FP services more effective. The current trial plans to assess the effectiveness of 3 counseling approaches in improving the uptake of modern contraceptives over a period of 6 months: sensitization, GATHER, and the BCS. The study hypothesis is that contraceptive uptake will differ among the 3 approaches.

The duration of the trial will be 8 to 9 months, structured in 3 phases. The first phase is a formative phase, during which baseline assessments will be obtained. This will be followed by the interventional phase, in which service providers will be given training specific to the study arm they are allocated to. The last phase will be an exploratory phase meant to identify enablers and barriers and other findings that can facilitate the scaling-up of the study. The conceptual framework of the study is shown schematically in Figure 1.

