### Data Collection and Analysis

Data has been collected from structured facility records and client exit interviews at baseline (before the intervention) and will be collected 3 and 6 months after the intervention. Data quality will be ensured through descriptive statistics and logical validation checks, identifying missing values, inconsistencies, and outliers. The baseline characteristics will be summarized for assessing comparability across clusters.

The quality of FP services will be assessed using the Quick Investigation of Quality tool, which measure 25 key indicators of counseling quality [27]. For the data analysis, SPSS (version 26; IBM Corp) will be used. Service provider and client characteristics will be summarized in descriptive analyses. Exploratory comparisons will use paired 2-tailed *t* tests (or Wilcoxon signed-rank tests), ANOVA, and *χ*^2^ tests.

Mixed effects regression models with a random intercept for hospital catchment (cluster) will be using for clustering. These will be used to analyze binary outcomes of the interventions, such as uptake of modern contraceptives. Mixed effects logistic regression will be applied. For continuous outcomes, such as client satisfaction and quality score, we will use mixed effects linear regression. To assess robustness, population-averaged models using generalized estimating equations with robust SEs will be considered as a sensitivity analysis.

To estimate the changes in outcome over time between the interventional and control arms, we will use a difference-in-differences approach. All multivariate models will be adjusted for individual-level covariates such as age, parity, education, and baseline contraceptive use, as well as facility-level characteristics.

Effect sizes for categorical outcomes will be reported as odds ratios with 95% CIs, and for continuous outcomes, Cohen *d* will be used. Statistical significance will be assessed at a 2-sided *P* value <.05. Results will be presented in the form of tables and graphical summaries for interpretability and for informing future scalability.

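### The stated inputs (1-sided 5%, 80% power, 25% vs 40%, design effect 1.38) do not give 60 per arm; the power of 60 is not reported, and the 1-sided basis conflicts with the 2-sided analysis

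*Protocol article*

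**What the plan says.** The section on purposive sampling and sample size states: "The sample size was calculated using a standard formula for comparing 2 populations through testing the 1-sided hypothesis". It sets alpha at 5% and power at 80%. For the effect, "we assumed values of 25% and 40% for contraceptive uptake in the control and interventional arms, respectively", a 15-point difference. It takes an ICC of 0.02, reports that a design effect of 1.38 was used, and gives the formula for it. It then calls the approach pragmatic, says that as a pilot the trial was not scaled up to confirmatory power, and ends: "a sample size of 60 per arm and 180 across all 3 arms was chosen". It reports neither the number that the formula yields nor the power of 60 per arm.

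Elsewhere, Study Framework says: "The study hypothesis is that contraceptive uptake will differ among the 3 approaches". Data Collection and Analysis says: "Statistical significance will be assessed at a 2-sided" P value below .05. Limitations warns only that a pilot might miss small effects.

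**The concern.** The section sets out alpha, power, effect, ICC and design effect, then gives a sample size. A reader would expect the size to come from the inputs, and it does not. Once the inputs are worked through, the reason given for departing from them (no inflation in a pilot) does not lead to 60 either. The test used for planning is also not the test planned for the analysis.

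The trial's aim is comparative effectiveness, significance tests are planned, and the Abstract expects the findings to help guide national family planning programmes. The article calls a 15-point gain its assumed effect, not a small one. If readers do not know that 60 per arm has well under even odds of detecting that gain, a non-significant result for GATHER or the BCS is easily over-read.

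**Working it through.** **Inputs, all from the sample size section:** p1 = 0.25, p2 = 0.40, difference 0.15, alpha = 0.05 (1-sided), power 0.80, ICC = 0.02, design effect (DE) 1.38, n = 60 per arm. The 2-sided rule is from Data Collection and Analysis.

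**Step 1. The design effect.** 1 + (m − 1) × 0.02 = 1.38 gives m = 20. At 60 per arm this implies 60 / 20 = 3 clusters per arm. The article's text states neither m nor the number of clusters, so this is an inference.

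**Step 2. The size that the inputs give.** Variance sum: 0.25 × 0.75 + 0.40 × 0.60 = 0.4275.

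- Unpooled, 1-sided: n = (1.645 + 0.842)² × 0.4275 / 0.15² = 117.5, so 118. Times 1.38: 162.1, so 163.
- Pooled, 1-sided (mean proportion 0.325): n = [1.645 × √(2 × 0.325 × 0.675) + 0.842 × √0.4275]² / 0.15² = 119.5, so 120. Times 1.38: 165.6, so 166.
- The same two formulas 2-sided (1.960 in place of 1.645): 149.1, so 150, and 152. With the DE: 205.8, so 206, and 210.

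The arcsine version lies between these, and a continuity correction raises n (133 1-sided, before the DE). No two-proportion variant tried gives 60.

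**Step 3. How 60 relates to these.** 60 / 118 = 0.51 and 60 / 120 = 0.50. Leaving out the inflation would leave 118 to 120, not 60. If the DE were already inside the 60, the underlying size would be 60 / 1.38 = 43.5, further still from 118. A one-sample 1-sided formula against a fixed 25% gives 56.2, so 57, which is near 60, but the article says that two populations are compared. Sixty is also exactly 120 / 2, as if a per-arm figure had been read as a two-arm total. The article supports neither explanation; both are only things for the sponsor to check.

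**Step 4. The power that 60 per arm gives, for 25% vs 40%.**

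- With the DE: SE = √(0.4275 × 1.38 / 60) = 0.0992, and 0.15 / 0.0992 = 1.513. 1-sided: Φ(1.513 − 1.645) = 0.447. 2-sided: Φ(1.513 − 1.960) = 0.327. The pooled versions are 0.439 and 0.318.
- Without the DE: SE = √(0.4275 / 60) = 0.0844, ratio 1.777. 1-sided 0.553, 2-sided 0.427. The pooled versions are 0.544 and 0.417.

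**Step 5. Precision and detectable difference (2-sided, with the DE).**

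- 95% CI half-width: 1.96 × 0.0992 = 0.194, about 19 points.
- Difference detectable with 80% power from 25%: 2.802 × √((0.1875 + 0.249) × 1.38 / 60) = 0.281, about 28 points (29 with the pooled formula).

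**The case against.** The best defence is the pilot disclaimer. A reader might infer that the article claims 80% power for 60 per arm. It does not: 80% is an input to a formula, and the text then cites feasibility and says that confirmatory power was not sought. That stands, so the fault is an unexplained derivation and an unreported power, not a false power claim. On the broadest reading, the disclaimer means that the formula was set aside. But then the calculation is not the basis for 60, and the design effect reported as used does not enter the number.

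Three further limits also stand.

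- The powers above are for an unadjusted comparison of two proportions at one time point. The planned analysis is a mixed model with difference-in-differences, adjusted for baseline use. Its power depends on correlations that the article does not give, and could be higher or lower.
- One could go further and compute power on the few degrees of freedom that three clusters per arm would leave. That count is inferred, and a t test is not the planned analysis, so it supports only a caution that the figures are optimistic if clusters are few.
- A reader might infer that the cited absolute increase of 8 to 18 points is wrong, because 30% to 40% is 5 to 15 points above the assumed 25%. The article states the increase against routine care in the cited review, and 30 − 8 = 40 − 18 = 22, so the figures are consistent with a 22% comparator. At most, that comparator differs from the 25% assumed here.

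The Limitations section and the cautious wording of the Conclusions reduce the risk of over-reading. They do not tell the reader that a 15-point gain is itself beyond what the trial can reliably detect.

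**Conclusion.** The point holds. Sixty per arm is half of the 118 to 120 that the stated inputs require before clustering, and a little over a third of the 163 to 166 required after it. Its power for 25% vs 40% is about 44-45% 1-sided and 32-33% 2-sided with DE 1.38, or about 54-55% and 42-43% without it. None of these readings comes near 80%. The 1-sided planning and the 2-sided analysis contradict each other on the face of the text.

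These figures assume the article's own rates, ICC and design effect, a normal approximation, a single pairwise comparison at one time point and no multiplicity adjustment. With few clusters or several comparisons they are optimistic. They do not show that 60 per arm is an unsuitable size for a pilot, only that the stated basis does not produce it.

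**What to change.** In the sample size section:

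- Remove the 80% power, 1-sided calculation as the basis for 60 per arm.
- State that 60 per arm was chosen for feasibility and that, for an unadjusted comparison of 25% vs 40% at 2-sided 5% with DE 1.38, it gives about 33% power, a 95% CI half-width of about 19 points, and a difference detectable with 80% power of about 28 points.
- Add that these figures are optimistic if clusters are few, and state m and the number of clusters per arm behind the 1.38.
- Reconcile the sidedness. The simplest way is to use 2-sided 5% here, to match Study Framework and Data Collection and Analysis.
- Leave the 8 to 18 point range as cited. If anything is added, note that it implies a comparator near 22%.

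In the analysis and conclusions, present the effectiveness comparisons as estimates with confidence intervals.

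The cost is wording only: no extra women and no change to the design. The stated power becomes less favourable. The Results section reports that no outcome data have been analysed, so as of that version the change could be made before any results are known.
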